### Secondary Analysis

This study is collecting extensive data on demographics; the prevalence of HSV-2 and HIV infections; uptake of biomedical, behavioral, and structural interventions; and risk factors for HIV and HSV-2 infections among AGYW who are out of school. Secondary analysis is planned to understand how structural factors influencing vulnerability to HIV infection influence the uptake of cash transfer and other interventions and to understand how cash transfer may impact risky sexual behavior. Analysis of the longitudinal data will also be performed to explore how cash transfer impacts indicators for change and ultimately changes the outcome measure over time. The generalized estimating equations will be used for causal analysis and to verify the abovementioned theory of change.

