### Aims and Objectives

The overall aim of this study is to determine the impact of cash transfer on risky sexual behavior among AGYW receiving biomedical, behavioral, and other structural interventions in Shinyanga region. The primary objective is to assess the impact of cash transfer on the incidence of HSV-2 after 18 months. Secondary objectives are to examine the impact of cash transfers on compensated sex (defined as sexual encounters motivated by exchange for money, material support, or other benefits) and intergenerational sex (defined as a sexual partnership between AGYW and a man 10 or more years older). Through a qualitative study, the study seeks to understand how the intervention impacts the structural and behavioral drivers of the HIV epidemic.

The theory of change guiding this assessment is presented in Figure 1. It presents the contextual factors contributing to the HIV vulnerability among AGYW, intervention components, outcome, and impact of the interventions. It is hypothesized that cash transfer will reduce risky sexual behavior and new HIV infections among AGYW by boosting their income and therefore increasing their consumption capacity and choices and savings and asset accumulation as well as mitigating the impact of shocks. This will, in turn, reduce risky sex including compensated and intergenerational sex, thereby contributing to a reduction in new STIs.

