### Randomization and Blinding

All clusters that fulfilled the eligibility criteria in the three councils (Kahama town, Msalala district, and Ushetu district) were first ranked by their size and matched by residence (rural vs urban areas) and presence/absence of HIV high-risk areas (mines, plantations, and fishing areas). Therefore, four strata (rural cluster in the high-risk area, urban cluster in the high-risk area, rural cluster in the low-risk area, and urban cluster in the low-risk area) were formed. A total of 15 matched clusters with similar size were selected randomly to participate in the study across the four strata. In each matched pair, one cluster was randomly selected to receive the intervention package, and the other was automatically assigned to receive the control package. Matching was done to minimize the between-community variance in HSV-2 incidence within the matched clusters. No blinding was performed in this study, as it was not possible to blind study participants, Sauti implementers, data collectors, and data analysts because the intervention provided (cash transfer) was known to study participants, implementers, and researchers. Figure 2 presents an overview of the study design.

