### Outcomes

End points are assessed at baseline and after every 6 months over the next 18 months. The primary outcome measure is the incident HSV-2 infection. Secondary outcome measures include HIV prevalence, reporting of intergenerational sex (sexual partnership between AGYW and a man 10 or more years older), and reporting of compensated sex (AGYW are asked to report whether they have received money or gifts in exchange for sex) in the last 6 months. Compensated sex is assessed by self-report of whether AGYW has had sex with anyone because they received money or gifts or because they expected to receive money or gifts. The primary exposure is cash transfer received. Table 3 presents the outcomes, indicators of change of outcomes, and uptake of interventions.

**Table 3 table3:** Outcomes, indicators of change of outcomes, and uptake of interventions.

Factor	Variables
Primary and secondary outcomes	Herpes simplex virus type 2 incidence, HIV prevalence, reporting of intergenerational sex, Compensated sex
Indicators for change	Increased comprehensive HIV prevention knowledge, increased income and savings, increased confidence to accept an HIV test, increased confidence to negotiate condoms with nonmarital partners, and increased access to biomedical interventions (community-based HIV testing and counseling services plus, sexually transmitted infection, gender-based violence, and substance and alcohol screening and family planning)
Uptake of Sauti interventions	Individuals who received interventions or control packages; within the intervention sites, individuals who received (1) SBCC^a^, cash transfer, WORTH+^b^ and (2) cash transfer and combination prevention interventions; and within the control sites, individuals who received (1) SBCC and WORTH+ and (2) combination prevention interventions

^a^SBCC: social and behavior change communication.

^b^WORTH+: Women Organizing Resources Together Plus.

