### Study Strengths and Limitations

This study has several strengths. First, the study incorporates both qualitative and quantitative data collection techniques to understand how cash transfer and other interventions synergistically mediate to reduce risky sexual behavior. Second, the study uses ACASI to collect sexual behavior and other sensitive data. Studies comparing face-to-face interviews with ACASI have reported that respondents are more likely to be open and honest when using ACASI [37,38]. Third, the study collects longitudinal data on biomedical, behavioral, and structural interventions on a large sample of AGYW (n=3120) who are out of school and therefore vulnerable to HIV infection to allow for the detection of the difference between arms. However, the study clusters are selected from Shinyanga region, which has a prevalence of HIV above the national average and may not be generalizable to other study regions with lower HIV prevalence in Tanzania.

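### The plan says GEE will verify the theory of change, but randomisation supports causal claims only for the effect of arm, not for the link from indicator to outcome

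*Protocol article*

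**What the plan says.** The Secondary Analysis section of the protocol article plans longitudinal work to "explore how cash transfer impacts indicators for change and ultimately changes the outcome measure over time". The next sentence gives the method and what it is meant to show: "The generalized estimating equations will be used for causal analysis and to verify the abovementioned theory of change".

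The theory is set out under Aims and Objectives as a two-step chain. In the first step cash works by "boosting their income and therefore increasing their consumption capacity and choices and savings and asset accumulation as well as mitigating the impact of shocks". In the second step: "This will, in turn, reduce risky sex including compensated and intergenerational sex, thereby contributing to a reduction in new STIs".

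Table 3, under Outcomes, lists the intermediate variables, beginning "Increased comprehensive HIV prevention knowledge, increased income and savings, increased confidence to accept an HIV test". On timing, the same section says: "End points are assessed at baseline and after every 6 months over the next 18 months".

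Randomization and Blinding shows what was allocated at random: "In each matched pair, one cluster was randomly selected to receive the intervention package". Study Strengths and Limitations gives as a strength that the data will help to "understand how cash transfer and other interventions synergistically mediate to reduce risky sexual behavior".

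**The concern.** Verifying the chain means showing that a change in income, savings or confidence causes a change in sexual behaviour. Nobody was randomised to savings or confidence. These indicators arise after allocation, and they plausibly share causes with behaviour, such as family support, temperament or local opportunity. GEE with robust standard errors deals with correlation between repeated measures and within villages. It does not deal with common causes.

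The plan therefore attaches to a named method a conclusion that the design does not support. The stake is the account of mechanism. A reader deciding which component to fund could be told that savings or confidence carried the effect when the data cannot separate that from a common cause.

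**Working it through.** **The plan's own figure.** No number in the article supports the pathway claim. The one design figure is power above 80% (Sample Size: 15 pairs, 70 per cluster, 20% v 13%, coefficient of variation 0.25, alpha 0.05, taken as two-sided). The matched-pair formula gives:

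c = 2 + (1.96 + 0.84)² × [0.20×0.80/70 + 0.13×0.87/70 + 0.25² × (0.20² + 0.13²)] / 0.07²
= 2 + 7.85 × [0.00229 + 0.00162 + 0.00356] / 0.0049
= 2 + 7.85 × 1.522 = 13.95 pairs.

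Fifteen pairs give power of 83.2%, so the figure reproduces. It concerns arm on HSV-2 and says nothing about the pathway.

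**What randomisation protects.**

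| Link | Protected by randomisation? |
|---|---|
| Assigned arm to indicator | Yes |
| Assigned arm to outcome | Yes |
| Indicator to outcome | No |

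An arm-only GEE can show that indicators and outcomes both moved. That pattern is equally compatible with cash acting on behaviour by another route. A GEE with indicators as covariates does estimate the third link, but with confounding. Neither version verifies the chain. The protection also applies to *assigned* arm, whereas the Outcomes section names receipt of cash as the primary exposure.

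**How large the confounding could be.** All settings below are assumptions. The true effect of indicator on outcome is zero throughout.

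*Set-up A: one round.* 30 villages × 70 women, 300 replicates per scenario, pair matching ignored. The indicator is binary and arm raises its log-odds by 0.5. Outcome log-odds at the reference are −1.4, so risk = 1/(1 + e^1.4) ≈ 20%. The village SD of outcome log-odds is 0.25. One standard-normal trait raises the indicator and lowers the outcome. The model is a logistic GEE (exchangeable, robust SE) on arm and indicator.

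| Trait log-odds (indicator / outcome) | Mean indicator OR | False link at p < 0.05 |
|---|---|---|
| 0 / 0 | 1.00 | 6% |
| +0.3 / −0.3 | 0.91 | 17% |
| +0.5 / −0.5 | 0.80 | 55% |
| +0.7 / −0.7 | 0.67 | 97% |
| +0.5 / −0.5, trait adjusted for | 1.00 | 3% |

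The arm-to-indicator and indicator-to-outcome tests were significant together in 6%, 17%, 55% and 97% of the unadjusted scenarios. The last row shows that the excess comes from confounding.

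*Set-up B: three rounds.* 30 villages × 60 women × 3 rounds, continuous indicator measured in the same round as the outcome, village SD 0.25. The trait has the stated correlation with the indicator and lowers the outcome log-odds by 0.2 or 0.4 per SD, which is an odds ratio of e^−0.2 = 0.82 or e^−0.4 = 0.67. Ranges cover separate runs.

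| Correlation of trait and indicator | Trait effect 0.2 | Trait effect 0.4 |
|---|---|---|
| 0.1 | 9% | 22% |
| 0.2 | 31% | 64% |
| 0.3 | 33–36% | 90–91% |
| 0.5 | 82–90% | 100% |

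With no confounding, runs gave 4% to 7%. At 100 replicates a rate of 33% has a simulation error of √(0.33 × 0.67/100) ≈ 5 points, so small differences between runs mean nothing. B gives higher rates than A for similar bias because three rounds supply more observations and so more precision around a biased estimate.

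**Does lagging with baseline adjustment cure it?** Only in part. At correlation 0.5, lagging the indicator one round and adjusting for baseline indicator and baseline behaviour lowered the false-link rate from 82% to 46% (trait effect 0.2) and from 100% to 94% (0.4). A stable unmeasured trait survives a lag.

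**The case against.** **The faulted model is inferred.** The article never says that indicators enter the GEE as covariates. The sentence before the quoted one can be read as arm on indicators and arm on outcomes by round, for which GEE is suitable. This stands: one cannot say that the plan prescribes a confounded regression. It does not rescue the word *verify*, because the arm-only model cannot test the middle link either.

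**GEE is only an estimator.** A reader might infer that GEE can never support a causal statement about a pathway. That is too strong. Weighted GEE is a standard way to fit a marginal structural model, and lags and adjustment fit within it. Whether the result is causal depends on exposure, timing, adjustment set and assumptions.

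**Missing detail belongs elsewhere.** A journal article may leave confounders, lags and sensitivity analyses to the full protocol or SAP, so their absence is not a fault here. The fault is the stated conclusion.

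**The error rates are assumed.** A reader might infer that the analysis would almost certainly report a false pathway. The documents do not support that. With weak confounding (correlation 0.1, effect 0.2) the rate was 9%, and nothing in the article fixes the strength.

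**Importance is limited.** The strengths section credits insight into mechanism to qualitative and quantitative data together, and Statistical Methods plans qualitative queries on how impact was achieved. Scale-up is tied to the trial's findings in general, not to this analysis. The section also uses *explore* one sentence earlier. All of this stands and keeps the point at secondary rank.

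**Conclusion.** The point holds in limited form. The article states that GEE will serve as causal analysis and verify a mediated theory, while the design randomises only village arm. Causal statements are protected for assigned arm on each indicator and on each outcome; the indicator-to-outcome link is open to confounding.

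If outcome is regressed on same-round indicators, the chance of declaring a non-existent link is about 5% without confounding. In the repeated-round layout it goes from roughly a third at correlation 0.3 and trait effect 0.2 to nearly all trials under stronger confounding. The single-round layout gives a lower start, 17% at its weakest non-zero setting, and ends at 97%. These figures rest on assumed confounder strength, about 20% outcome risk in set-up A, and an unadjusted model that the article does not spell out. They show what could happen, not what will.

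The primary HSV-2 comparison is unaffected. The change is worth making because it is cheap and concerns a claim the authors list among the study's strengths.

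**What to change.** 1. Confine causal statements from GEE to the effect of *assigned* arm on each indicator and each outcome, by round.
2. In the Secondary Analysis section, change *verify* to *explore*, and drop *causal* for the indicator-to-outcome link.
3. Analyse that link with the indicator one round ahead of the outcome (6-month indicator with 12-month behaviour, 12-month with 18-month), adjusted for baseline indicator, baseline behaviour and measured confounders. A weighted GEE or a mediation model would do.
4. Add a sensitivity analysis showing how strong an unmeasured common cause would have to be to explain the estimated link. This is needed because adjustment alone does not remove the bias, and a mediation model does not escape the assumption of no unmeasured confounding either.

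The planned survey rounds already supply the data. The costs are more analysis work, wider intervals (partly because lagging uses fewer round-to-round comparisons) and a weaker claim about mechanism.

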### Retention

To ensure that research participants recruited into the study are retained, the study developed strategies to optimize retention and minimize attrition rate. First, all participants in the intervention and control communities were given phones for maintaining regular contact with researchers. Second, a detailed and thorough explanation of the study visit timeline (baseline and all follow-up rounds) was given during the informed consent process. Third, during enrollment, participants were requested to provide phone numbers of their friends or relatives to facilitate tracing in the follow-up surveys. The phone numbers were updated in the follow-up rounds. Short text messages were sent before and during the time of data collection to remind and emphasize the importance of study participation in the success of the study. Fourth, the research team is working closely with CSOs, which train and support AGYW. AGYW receiving Sauti interventions in the village are trained and supported by 1-3 empowerment workers who are employees of the CSOs.

### Safety Monitoring

Given that this is an impact-evaluation study conducted among participants receiving Sauti’s standard biomedical, behavioral, and structural interventions, an interim analysis is not planned. For the same reason, a data and safety monitoring board is not established. This idea was approved by the institutional review boards, which granted ethics approval to the study. It is anticipated that any harm to AGYW as a result of study participation will be minimal. The study adheres to all safety guidelines established by Sauti program in defining and reporting social harm events. The social harm events resulting from study participation are closely monitored; recorded in the social harm event form; and reported to the Sauti program, CSOs, and the study principal investigator who initiates further investigations and responses, as appropriate.

### Auditing

Members of the study team, representatives of the CSOs implementing the study, and the sponsor conduct regular auditing of the study activities. During auditing, a review of the informed consent forms and study-related materials and procedures is performed to ensure that informed consent forms are thoroughly and accurately filled and that all the consenting procedures are strictly adhered to. A review of study-related materials and procedures is performed to ensure that the study is conducted and reported in compliance with the protocol, good clinical practices, and ethics requirements.

### Ethics

This study was approved by the Medical Research Coordinating Committee of NIMR in Tanzania (NIMR/HQ/R.8c/Vol.II/841) and institutional review board of the Johns Hopkins University (IRB00007976). Approval to conduct the study in the study communities was also provided by regional and district authorities as well as community leaders.

All AGYW graduating from SBCC sessions in the study clusters are informed about the study in group introductory session, and study information was provided in oral and written forms using Swahili language. Girls who required consent from parents/guardian were advised to bring their parents/guardians, if interested in study participation. All girls younger than 18 years of age required consent from parents/guardian and their assent to participate in the study, except for emancipated minors (ie, minors who are married, have given birth or demonstrating full independence, eg, living alone or heading the household). If a mature participant or guardian is illiterate, the consent procedure is conducted in the presence of a witness who is literate and not related to the study. AGYW willing to participate received further information on a one-to-one basis in a confidential environment guided by the participant information and informed consent form. As part of the consent process, study staff explained the study aims, procedures, any inherent risks or benefits, and their right to decline study participation or terminate participation in the study at any time, without giving reasons and affecting their health care or participation in the CT program provided by Sauti. Participants and their parents/guardians were given time to discuss participation and raise any additional questions. Consent to study participation was documented using a written consent form before any study-related data collection. Illiterate participants and parents/guardians provided a thumbprint in the presence of a witness who signed the consent.

### Confidentiality

AGYW’s names, their telephone numbers, and any locator information collected that identifies them are kept confidential and always under lock and key whenever not in use. Only study personnel involved in data collection have access to locator information. Locator information is only used to ensure validation of the identity of the participant in follow-up visits and for contacting the participant for participation in the follow-up rounds.

A unique study identification number and the encrypted Sauti routine identification (SRI) number (participant unique identifier of the Sauti program) are collected using the study tools and hence captured in the database. The SRI number is encrypted before it is used for study purposes of maintaining the confidentiality of participant’s information. Although the study number is used to identify the dataset for an individual participant in the study dataset, the SRI is used to link study data collected and routine data obtained from the program.

### Participants and Public Involvement

This is an impact evaluation study of the interventions provided by Sauti project. AGYW were involved in the design of this study through their representative CSOs. The involvement included advising on the content of the study materials, data collection techniques such as the use of PGDs, and techniques that enhance confidentiality and anonymity (eg, ACASI). CSOs were also crucial in the recruitment of study participants and are involved in monitoring study activities and tracing of study participants. They will also be involved during the dissemination of the findings at the community and regional level.

During the development of interventions, the Sauti project involved intensive dialogues with local leaders, Ministry of Health, Community Development, Gender, Elderly and Children, Tanzania Social Action Fund, National AIDS Control Program, Tanzania Commission for HIV/AIDS, Tanzania Communications Regulatory Authority, mobile communication companies, CSOs, and AGYW representatives among other national and international stakeholders. These dialogues led to the development of the combination prevention interventions offered by the project to AGYW, including the cash transfer amount and payment modality.

## Results

The study was funded in June 2017, and the enrollment took place in December 2017. The baseline study was conducted among AGYW who consented for study participation, and study participants were followed up for 18 months. Follow-up study assessments are conducted 6, 12, and 18 months postintervention initiation. A total of two rounds of the follow-up surveys postintervention are complete, and one round has not yet been performed. The results are expected in December 2019 and will be disseminated through conferences and peer-reviewed publications.

## Discussion

### Overview

This cluster randomized trial intends to evaluate the impact of cash transfer in the presence of combination prevention interventions in the reduction of risky sexual behavior. Previous trials in sub-Saharan Africa were conducted to assess the effect of cash transfer [23,28], but none were conducted among out-of-school girls to ascertain the synergetic impact of cash transfer, WORTH+ interventions, and biomedical and behavioral interventions.

### Study Strengths and Limitations

This study has several strengths. First, the study incorporates both qualitative and quantitative data collection techniques to understand how cash transfer and other interventions synergistically mediate to reduce risky sexual behavior. Second, the study uses ACASI to collect sexual behavior and other sensitive data. Studies comparing face-to-face interviews with ACASI have reported that respondents are more likely to be open and honest when using ACASI [37,38]. Third, the study collects longitudinal data on biomedical, behavioral, and structural interventions on a large sample of AGYW (n=3120) who are out of school and therefore vulnerable to HIV infection to allow for the detection of the difference between arms. However, the study clusters are selected from Shinyanga region, which has a prevalence of HIV above the national average and may not be generalizable to other study regions with lower HIV prevalence in Tanzania.

